# Continuous passive paracentesis versus large-volume paracentesis in the prevention and treatment of intra-abdominal hypertension in the critically ill cirrhotic patient with ascites (COPPTRIAHL): study protocol for a randomized controlled trial

**DOI:** 10.1186/s13063-023-07541-4

**Published:** 2023-08-15

**Keywords:** Abdominal perfusion pressure, Abdominal compartment syndrome, Outcome, Acute kidney injury, Renal failure, Multi-organ failure, Randomized controlled trial

## Abstract

**Background:**

Critically ill patients with cirrhosis and ascites are at high risk for intra-abdominal hypertension (IAH) which increases mortality. Clinical guidelines recommend maintaining intra-abdominal pressure (IAP) below 16 mmHg; nonetheless, more than three quarters of critically ill patients with cirrhosis develop IAH during their first week of ICU stay. Standard-of-care intermittent large-volume paracentesis (LVP) relieves abdominal wall tension, reduces IAP, optimizes abdominal perfusion pressure, and is associated with short-term improvement in renal and pulmonary dysfunction. However, there is no evidence of the superiority of different paracentesis strategies in the prevention and treatment of IAH in critically ill patients with cirrhosis.

This trial aims to compare the outcomes of continuous passive paracentesis versus LVP in the prevention and treatment of IAH in patients with cirrhosis and ascites.

**Methods:**

An investigator-initiated, open label, randomized controlled trial, set in a general ICU specialized in liver disease, was initiated in August 2022, with an expected duration of 36 months. Seventy patients with cirrhosis and ascites will be randomly assigned, in a 1:1 ratio, to receive one of two methods of therapeutic paracentesis. A stratified randomization method, with maximum creatinine and IAP values as strata, will homogenize patient baseline characteristics before trial group allocation, within 24 h of admission.

In the control group, LVP will be performed intermittently according to clinical practice, with a maximum duration of 8 h, while, in the intervention group, continuous passive paracentesis will drain ascitic fluid for up to 7 days.

The primary endpoint is serum creatinine concentration, and secondary endpoints include IAP, measured creatinine clearance, daily urine output, stage 3 acute kidney injury and multiorgan dysfunction assessed at day 7 after enrollment, as well as 28-day mortality rate and renal replacement therapy-free days, and length-of-stay. Prespecified values will be used in case of renal replacement therapy or, beforehand ICU discharge, liver transplant and death. Safety analysis will include paracentesis-related complication rate and harm. Data will be analyzed with an intention-to-treat approach.

**Discussion:**

This is the first trial to compare the impact of different therapeutic paracentesis strategies on organ dysfunction and outcomes in the prevention and treatment of IAH in critically ill patients with cirrhosis and ascites.

**Trial registration:**

ClinicalTrials.gov NCT04322201. Registered on 20 December 2019

**Supplementary Information:**

The online version contains supplementary material available at 10.1186/s13063-023-07541-4.

## Introduction

### Background and rationale {6a}

Chronic liver disease patients with cirrhosis and ascites are at high risk for increased intra-abdominal pressure (IAP), and both the presence and the duration of intra-abdominal hypertension (IAH) are known independent risk factors for mortality in the critically ill patient [1, 2].

The prevalence of IAH and abdominal compartment syndrome (ACS) is very high among critically ill patients with liver cirrhosis when compared to other mixed populations of intensive care patients [3–5]. In the setting of IAH, paracentesis reduces abdominal wall tension and improves overall intra-abdominal hemodynamics by minimizing IAP and optimizing abdominal perfusion pressure (APP) of intra-abdominal organs [1].

Clinical practice guidelines for the critically ill patient with IAH/ACS, based on expert opinion, recognize liver dysfunction/cirrhosis with ascites as a risk factor and suggest the evacuation of obvious intra-peritoneal fluid with the use of percutaneous catheter drainage as part of a stepwise medical management algorithm to reduce and maintain IAP < 16 mmHg [1]. Nonetheless, IAH develops in more than three quarters of critically ill patients with cirrhosis during their first week of ICU stay [4, 5].

Therefore, a strategy for the prevention and treatment of IAH/ACS could improve patient outcomes in the critically ill cirrhotic patient by minimizing IAP and optimizing APP and potentially leading to improved multi-organic function. In fact, some studies in intensive care have shown that LVP is safe and associated with short-term improvement of renal, pulmonary, and hepatic dysfunction, although follow-up and clinical outcomes in the ICU were not assessed [4, 6–10]. Furthermore, therapeutic large-volume paracentesis (LVP) is the standard-of-care in the treatment of tense ascites and hepato-renal syndrome (HRS) in acutely decompensated liver cirrhosis patients [11–14]. An experimental study has demonstrated causality between small increases of IAP (5–10 mmHg), after merely 24 h, and the development of acute renal injury in HRS [15]. However, the recommendation for paracentesis in the treatment of IAH/ACS is based on low-quality evidence [1] and, to the best of our knowledge, there are no studies comparing different therapeutic paracentesis strategies in the critically ill cirrhotic patient with IAH [1].

### Objectives {7}

#### General objective

The general aim of this trial is to assess the impact of IAH on organ disfunction and clinical outcomes in the critically ill cirrhotic patient with ascites.

#### Specific objective

The objective of this trial is to compare the outcomes of two different methods of therapeutic paracentesis used in our clinical practice in the prevention and treatment of IAH, specifically, regarding the impact on renal function, as well as respiratory, neurological, cardiovascular, hematological, and hepatic functions, in addition to 28-day mortality and ICU length-of-stay (LOS).

## Trial hypothesis

A continuous passive paracentesis (CPP) strategy in the treatment of IAH improves organ dysfunction and clinical outcomes when compared to standard LVP in the critically ill cirrhotic with ascites.

## Methods

### Trial design {8}

#### Trial design

This is an investigator-initiated, single-site, open label, randomized clinical trial with parallel group allocation ratio of 1:1 to assess for efficacy and safety.

## Participants, interventions, and outcomes

### Study setting {9}

#### Trial settings

This trial is set in a general intensive care unit (ICU) specialized in liver disease at Hospital de Curry Cabral, Centro Hospitalar Universitário Lisboa Central (CHULC), Lisboa, Portugal, a tertiary university hospital, with an expected duration of 36 months.

### Eligibility criteria {10}

#### Population of interest

The critically ill patient presents with a life-threatening condition that requires pharmacological and/or mechanical support of vital organ functions﻿. The population of interest is the critical cirrhotic patient with ascites and acute decompensation admitted in the ICU.

#### Patient eligibility

All patients with liver cirrhosis admitted in the ICU stay are eligible for this trial.

#### Inclusion criteria

Inclusion criteria are defined by the following:Adult patient (≥ 18 years old),Diagnosis of liver cirrhosis andPresence of ascites grade ≥ 2 [12].

#### Exclusion criteria

Exclusion criteria are defined by the following:Extreme age (≥ over 75 years old),Acute surgical condition or laparotomy in the preceding 4 weeks,Previous liver transplant,Hemorrhagic ascites (red blood cells count > 10,000/mL) [16],Extreme clinical severity (APACHE II ≥ 34),Any of the following conditions present 24 h after admission:aHemorrhagic shock with active uncontrolled bleeding,bRefractory shock (mean arterial pressure < 65 mmHg) despite multiple vasopressor support,Predictably short (< 72 h) ICU stay andTherapeutic futility determined by the medical staff.

Notes:These criteria are to be applied independently of any previous treatments of ascites, including recent LVP (i.e., in the emergency department before ICU admission), andExamples of “predictably short (< 72 h) ICU stay, precluding patient enrolment, may be, i.e., the reversal of clinical instability after initial therapy and adequate resuscitation in the ICU, such as < 6 h of vasopressor support; variceal bleeding controlled in the ICU without developing organ failure; or prompt reversal of oliguria/AKI.

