#### Safety procedures and assessment

Clinical management will comply with current guidelines, including strict prevention, detection, and treatment of paracentesis-related complications, including paracentesis associated circulatory dysfunction, hypovolemia, intra-abdominal organ perforation and bleeding, catheter-related abdominal wall infection, and secondary peritonitis and abdominal wall fistula or bleeding [12]. Paracentesis-related complications and harm will be actively screened and reported by clinicians.

Paracentesis associated circulatory dysfunction is prevented with standard-of-care intravenous 20% albumin infusion (8 g for each 1 l of drained ascitic fluid) administered to all patients and, additionally, crystalloid infusion may be indicated by the attending physician to strictly avoid hypovolemia [12].

Intra-abdominal organ perforation and bleeding are prevented with (a) ultrasound guided paracentesis and (b) coagulopathy treatment, mandatory in case of severe thrombocytopenia (platelet count < 50,000/mL) or hypofibrinogenemia (< 0.7 g/L), as clinically indicated by the attending physician or the Blood Transfusion department [23–27].

Catheter-related abdominal wall infection and secondary peritonitis are to be prevented with aseptic paracentesis technique and standard catheter point of insertion surveillance for signs of inflammation or infection, similar to central venous catheter procedures [28].

We do not use prophylactic antibiotics along with the indwelling abdominal paracentesis catheter (IAPC) in the CPP intervention group nor in the control group.

The definition of secondary peritonitis includes the following: (1) polymorphonuclear cell count elevation > 50% in 48 h after the initial paracentesis or (2) microbiologic “de novo” isolation of bacteria after 48 h after paracentesis.

In case of isolated bacterial culture of suspected skin contaminants, without signs of infection, a new direct ascitic tap at a different site should be performed to confirm or exclude a diagnosis of secondary peritonitis.

Whenever a clinical diagnosis of secondary peritonitis is considered, then antibiotic treatment should be immediately started according to standard clinical practice.

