### Sample size {14}

The sample size was calculated using the statistical noncentral *t *function, with a one-sided alpha level of 0.05 [31]. The calculations were based on the expected renal function and IAP variation between groups, since we assume the former to be dependent of the latter.

To support the trial rationale of an expected clinically significant IAP decrease of 3 mmHg in the intervention group, a total of 44 patients are considered necessary to detect a statistically significant difference, with 1:1 allocation ratio, 80% statistical power, and 95% confidence level. This estimate is based in a post-hoc analysis of 61 patients with cirrhosis from a multicentric randomized controlled trial in shock patients where a mean difference in IAP of 3 mmHg was found between survivors and non-survivors (13.7 ± 3.9 and 16.7 ± 3.9 mmHg, respectively) [4].

Regarding the primary outcome, to detect a clinically and statistically significant decrease in serum creatinine of 0,4 mg/dL in the intervention group, a total of 60 patients is estimated, with a 1:1 allocation ratio, 95% statistical power, and 95% confidence. This estimate is based on a multicentric observational study of acutely decompensated patients with cirrhosis. In this study, cirrhotic acute-on-chronic liver failure patients with at least one organ failure had a mean creatinine difference of 0,4 mg/dL between survivors and non-survivor groups (0.9 ± 0.45 and 1.3 ± 0.48 mg/dL) [32].

We arbitrarily estimate that protocol non-adherence/attrition or violation after randomization may affect approximately 15% of cases and, therefore, to ensure that the number of patients that complete the protocol is reached for the primary outcome, the total sample size is set at 70 patients with a 1:1 group allocation ratio.

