## Data collection and management

### Plans for assessment and collection of outcomes {18a}

The assessment and collection of trial data will start at patient enrollment (D0) including vital signs, specific therapies (i.e., albumin, transfusions), vital organ support, blood, urine, and ascitic fluid tests, repeatedly up to D7.

The trial protocol includes the daily collection of an 8-h (480 min) urine volume, at blocked nocturnal interval from 23 to 07 h, for measurement of creatinine clearance, based on the following formula: creatinine clearance (mL/min) = (urinary creatinine [mg/mL] × urine volume [mL])/(serum creatinine [mg/mL] × urine collection time [480 min]) [34].

Daily blood analysis includes complete hemogram, coagulation, and biochemistry and arterial blood gas. Ascitic fluid will be collected with every new paracentesis and repeated every 48 h in the intervention group for screening of infectious complications.

Collected trial variables are mainly included in clinical severity scores APACHE II [35], SAPS II [36], CLIF-C ACLF [37], CLIF-SOFA, SOFA [38], RIFLE [30], KDIGO [29], ICA-AKI [13], MELD [39], and MELD-Na [40] and incorporate liver disease etiology, precipitant event for critical illness, urine output, serum creatinine, estimated and measured creatinine clearance, and number of days on RRT, Glasgow coma score and West-Haven scale, number of days under vasopressor support and dosage, PaO_2_/FiO_2_ ratio, positive end-expiratory pressure and number of days under mechanical ventilation, total bilirubin, coagulation international normalized ratio, platelet count, arterial blood lactate and prescribed albumin dosage. Intermediate effect variables IAP and APP will be measured throughout ICU stay to test the trial rationale.

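### The red-cell exclusion and the platelet threshold are printed per mL, which makes them 10 and 50 cells per µL; neither fits the condition it names

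*Protocol article*

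**What the plan says.** Under Eligibility criteria {10}, the exclusion criteria in the protocol article list "Hemorrhagic ascites (red blood cells count > 10,000/mL) [16"]. The notes to that list add: "These criteria are to be applied independently of any previous treatments of ascites, including recent LVP". A puncture shortly before ICU admission therefore does not waive the criterion.

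Under Safety procedures and assessment, coagulopathy treatment is described as "mandatory in case of severe thrombocytopenia (platelet count < 50,000/mL"), with a fibrinogen limit alongside.

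Each threshold appears once. Neither is given in any other unit elsewhere in the article.

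Under Concealment mechanism {16b}, the attending physicians check the inclusion and exclusion criteria and decide eligibility before the envelope is opened.

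**The concern.** An exclusion labelled haemorrhagic ascites should separate bloody fluid from ordinary ascites. At 10 red cells per µL it cannot do so, because a minute amount of blood from the tap itself passes the limit. The platelet threshold shows the same pattern: 50 per µL is practically no platelets, so it does not work as a limit for severe thrombocytopenia. Two blood-cell counts in separate sections, both about 1,000-fold out of scale for what they name, point to an error in the volume unit rather than to a deliberately strict rule.

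What is at stake is whether the stated criteria describe the enrolled population. A physician who follows the print has to exclude a patient whose available sample carries trace blood. A physician who reads the number in another unit applies a limit that is not written down, and a patient enrolled that way may count as an eligibility violation when checked against the protocol. The article gives no rule for a blood-contaminated sample that would settle such cases.

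**Working it through.** The red-cell limit is a cited cut-off, not a derived figure, so there is no calculation of the plan's own to reproduce. The check is a unit conversion followed by a dilution.

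**Inputs from the article**
- Red-cell exclusion: 10,000 per mL (Exclusion criteria).
- Platelet threshold: 50,000 per mL (Safety procedures and assessment).

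**Assumptions, not in the article**
- Red-cell count of blood: 2 to 5 million per µL.
- Sample volume: 10 mL, that is 10,000 µL.

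**Step 1, conversion (1 mL = 1,000 µL)**
- Red cells: 10,000 / 1,000 = 10 per µL.
- Platelets: 50,000 / 1,000 = 50 per µL.

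**Step 2, blood needed to reach the red-cell limit**

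Blood fraction = limit per µL / red cells per µL of blood. Volume in the sample = fraction × 10,000 µL.

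| Assumed red cells per µL of blood | Blood fraction at the limit | Blood in a 10 mL sample |
|---|---|---|
| 2 million | 10 / 2,000,000 = 5 per million | 0.05 µL |
| 3 million | 3.3 per million | 0.033 µL |
| 5 million | 10 / 5,000,000 = 2 per million | 0.02 µL |

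The conclusion is the same across the range: a trace of blood reaches the limit.

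**Step 3, scale of the ambiguity**

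The same number read per µL would be 1,000 times higher and would need 20 to 50 µL of blood in 10 mL. This shows only how far apart the two readings lie, not which one is intended.

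**Step 4, is mL used in some special sense?**

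No. The clearance formula under Plans for assessment and collection of outcomes {18a}, "urinary creatinine [mg/mL] × urine volume [mL])/(serum creatinine [mg/mL] × urine collection time [480 min"]), gives (mg/mL × mL) / (mg/mL × min) = mL/min. The unit is used there in its ordinary meaning and is dimensionally consistent.

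**Step 5, can the number of patients affected be found?**

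No. The article gives no distribution of ascitic red-cell counts, no rate of blood-contaminated taps and no screening yield. For a purely assumed excluded share p, the number of otherwise eligible patients needed to randomise 70 is 70 / (1 − p). That is 78 at p = 10% (70 / 0.9 = 77.8), 140 at 50% and 700 at 90%. The article does not narrow this range.

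**The case against.** A reader might infer that the criterion shuts out much of the target population and puts recruitment of 70 patients in 36 months at risk. The article does not support that. Step 2 shows how little blood reaches the limit, not how many patients exceed it. The inference also requires staff to follow the printed unit, and physicians in an ICU specialised in liver disease have the label and the reference to guide them. Nothing shows that the criterion was applied literally or that it has limited recruitment.

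The text also mandates no diagnostic tap before randomisation. Fluid collection is described within the allocated procedures, and trial data collection, including ascitic fluid tests, starts at enrolment. The literal rule can therefore affect only patients who already have a red-cell count.

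Nor does the error bias the treatment comparison. Eligibility is settled before allocation by physicians blinded to the allocation blocks. The trial has one site, so differences between sites do not arise; only differences between physicians could, and none is documented.

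Finally, a µ may have become an m when the text was converted. No µ occurs anywhere in the text, so this cannot be tested directly. It is possible but less likely: the unit recurs in two separate sections of otherwise clean text, and the Greek α under Statistical methods {20a} came through intact.

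These points limit the size of the problem. They do not make the printed threshold fit its label, and relying on physicians to see past the unit concedes that the criterion cannot be used as written.

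**Conclusion.** The concern holds as an error in the stated unit of an eligibility threshold, with the same error in a safety threshold. The conversion to 10 and 50 cells per µL is exact. That trace blood exceeds the red-cell limit rests on an assumed 2 to 5 million red cells per µL of blood and holds throughout that range. The consequence is an exclusion that is either unworkably strict for patients with an available sample or replaced in practice by an unwritten limit.

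The number of patients affected is unknown and cannot be derived. The sample-size calculation is untouched, since it uses creatinine and intra-abdominal pressure only. The damage is to the description of the enrolled population and to the record of eligibility compliance.

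**What to change.** 1. Look at the published page to confirm that the unit is printed per mL in both places.
2. Check the red-cell threshold and its volume unit against reference [16], and restate the exclusion in the unit the site laboratory reports for ascitic fluid.
3. Notify the Research Center and the Ethics Committee, as the protocol requires for any modification.
4. Confirm from the screening log which reading physicians used, and report any patient whose eligibility depends on the unit.
5. Reconcile the platelet unit under Safety procedures and assessment with the sources cited there. No view is taken here on which clinical threshold is right.

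The cost is a short text correction, one notification and a review of existing screening records. No new procedure or data collection is needed.

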### Who will take informed consent? {26a}

The informed consent (Supplemental file 1) will be obtained by the attending physician from the proposed trial participant or authorized surrogate. In the particular case where the patient is not clinically able to decide (i.e., sedation or encephalopathy), and an authorized surrogate is not available, the Ethics Committee allowed for a presumed form of patient consent to participate in the clinical trial, based on public interest in the results of this study. The Principal Investigator (P.I.) and another ICU professional will endeavor any reasonable means to contact the authorized surrogate and provide written proof. Additionally, if at any time the patient, or it is authorized surrogate, is able to decide, then he/she may choose to withdraw consent to participate and be removed from the trial.

### Additional consent provisions for collection and use of participant data and biological specimens {26b}

There are no provisions for additional consent for ancillary studies using data not included in the original study protocol. Ancillary studies requiring additional data collection will be treated and conducted as independent studies.

## Interventions

### Explanation for the choice of comparators {6b}

This trial compares two methods of therapeutic paracentesis, namely, CPP versus standard-of-care LVP in the prevention and treatment of IAH. The CPP is expected to improve ascitic fluid drainage, therefore, providing better prevention and treatment of IAH, rather than intermittent LVP, which allows for the periodical accumulation of ascites with the potential deleterious effects of intermittent increases of IAP.

### Intervention description {11a}

The measurements of IAP will be performed every 6 to 8 h according to our center’s monitoring protocol (Supplementary file 2) and our clinical practice regarding the management of specific thresholds of IAP follows the current clinical guidelines to titrate therapy to maintain IAP less than 16 mmHg [1].

